##### Differential treatment response: four potential moderators

To gain more insight into differential treatment response, we will first examine which of the potential predictors, nominated in interviews by expert clinicians and based on the literature (see Table 3), actually predict (differential) treatment response. We will adopt the Personalized Advantage Index analysis developed by DeRubeis [27] that was previously used in the research group of the Principal Investigator [19, 20]. We will first build four univariate regression models for each predictor, with the predictor and separate variables for the interaction with the three interventions (moderators). We will then build a multivariable regression model with all four predictors and separate variables for the predictors and their interaction with the three interventions, to examine the relative contribution of each potential predictor or moderator. The outcome variable is the ADP-IV. In addition, we plan to also do a data-driven approach, in which we use machine learning techniques to select the moderators that go into the Personalized Advantage Index algorithm.

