#### Potential predictors and moderators

The selection of potential predictors or moderators to be examined was determined in consultation with experts:Inventory of Personality Organization (IPO-83-NL, [50]). The IPO is a self-report instrument consisting of 83 items on a 5-point Likert scale, based on Kernberg’s structural model of personality organization [21]. The Dutch version of the IPO has three main scales (Identity Diffusion, Primitive Defence and Reality Testing) and two supplementary scales (Aggression and Moral Values). The IPO-83-NL has good reliability and validity and appears to be a useful instrument to measure general personality pathology [15].Childhood Trauma Questionnaire-Short Form (CTQ-SF, [17]). This self-report measurement assesses childhood trauma. The short form was developed from the original 70-item version [16] and consists of 28 items measuring physical, sexual and emotional abuse and physical and emotional neglect. Its reliability and criterion-related validity have been established [17]. A recent study in the Netherlands confirmed its five-factor model [92].Nederlandse Narcisme Schaal (NNS, [34]). The NNS measures three dimensions of narcissism: overt (‘centrifugal’) narcissism and covert (‘centripetal’) narcissism and isolation. The questionnaire consists of 35 items with a 7-point Likert scale. Covert narcissism is hypothesized to be present in some patients with a Cluster-C PD and could possibly influence the outcome. The construction of this subscale is based on the Dutch translation of the hypersensitive narcissism scale [47] and consists of 11 items, with good reliability (Cronbach’s alpha .82). Dutch norms are available, although further research is necessary.Autism Spectrum Quotient short form (AQ-10). The AQ-10 Adult is derived from the original 50-item AQ [2], by a selection of the 10 items with the best discriminant validity. The questionnaire consists of 10 statements with for every statement four response options: strongly agree, slightly agree, slightly disagree, strongly disagree. At a cut-point of 6, sensitivity was .88, specificity was .91 and positive predictive value was .85.

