### Participant timeline {13}

#### Sample size {14}^3^

First, the required sample size was calculated to compare the three types of active treatments. Three pairwise comparisons will be conducted between the active treatment arms (ST vs. APT, ST vs. SPSP; APT vs. SPSP). We want to detect a medium effect size (*f*=0.11) in a pairwise comparison of pre-post change between two active treatment arms, equivalent to *f*(*v*)=.2460 and Cohen’s *d*=.492, with Bonferroni-corrected *p* = 0.0167, a power of 0.80 and within-person correlation coefficient=0.60, for which 88 patients are needed per arm. Because three types of therapies will be compared, 3 × 88 = 264 participants are needed to perform three pairwise comparisons. We chose a medium effect size (f=0.11^4^) since this would also be a clinically meaningful difference, as opposed to a smaller effect size.

The correlation of 0.60 is an educated guess of the correlation between repeated assessments based on the previous RCTs the authors conducted.

The final analysis will be conducted with mixed regression on time series: the change in slope over time between two treatments. Because power analysis for mixed regression are complex and based on complex assumptions about the covariance-structure, a simplified approach was chosen by conducting a power analysis on the pre-post change.

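### The predictor and moderator models list no baseline ADP-IV term and leave the form of the ADP-IV outcome open, so markers of starting severity can pass as predictors of response

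*Protocol article*

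**What the plan says.** The subsection on differential treatment response in the protocol article (Statistical methods {20a}) aims to find which candidate variables predict treatment response, overall or differentially. It lists the model terms twice. For the single-predictor models: "We will first build four univariate regression models for each predictor, with the predictor and separate variables for the interaction with the three interventions (moderators". The multivariable model then holds all four predictors and their interactions with the interventions. On the outcome it says only: "The outcome variable is the ADP-IV".

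The four specific predictors are set out under Potential predictors: childhood trauma, autism traits, personality organization and vulnerable narcissism. Severity of the PD appears there too, but in a separate list of general predictors. Of the instrument for personality organization, the protocol says: "The IPO-83-NL has good reliability and validity and appears to be a useful instrument to measure general personality pathology".

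The sample size section sizes the pairwise treatment comparisons: "a simplified approach was chosen by conducting a power analysis on the pre-post change". It adds: "The correlation of 0.60 is an educated guess of the correlation between repeated assessments".

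**The concern.** The four candidates are all presented as bound up with personality pathology, the IPO most directly. They can therefore be expected to correlate with the ADP-IV at baseline. If baseline ADP-IV is not in the model, that correlation has to go somewhere.

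- **Follow-up score as outcome.** Patients who start worse tend to end worse, so a severity marker appears to predict poor response.
- **Change score as outcome.** Patients who start worse tend to fall further by regression to the mean, so the same marker appears to predict good response.

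Identifying predictors is the trial's third aim. As the text stands, both the existence and the direction of a predictor could turn on a choice of score that is not fixed. The moderator tests have a different problem: variance that baseline would explain stays in the residual and costs power, in a trial that was not sized for interactions.

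**Working it through.** **Inputs from the protocol article (Sample size).** "We want to detect a medium effect size", given as f = 0.11, f(V) = 0.2460, d = 0.492; "with Bonferroni-corrected *p* = 0.0167"; "a power of 0.80 and within-person correlation coefficient=0.60, for which 88 patients are needed per arm"; 264 in total.

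**Assumptions.** The correlation r between a marker and baseline ADP-IV is not in the documents; 0.1 to 0.5 is shown. Tests are two-sided at 0.05, arm main effects are included, and baseline and follow-up have equal variance (SD 1).

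**1. The plan's own figure.** f(V) = 0.11 × √(2/(1 − 0.60)) = 0.2460 and d = 2 × 0.2460 = 0.492, as stated. The noncentral F test of group by time at alpha 0.0167 gives power 0.795 with 87 per arm and 0.800 with 88. The 88 reproduces, as a calculation on pre-post change with correlation ρ = 0.60.

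**2. Residual SD of the three analyses at ρ = 0.60.**
- Follow-up score, no baseline: 1.000
- Change score: √(2(1 − 0.60)) = 0.894
- Follow-up score with baseline as covariate: √(1 − 0.60²) = 0.800

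Relative to the follow-up score alone, the baseline term removes 0.60² = 36% of the residual variance.

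**3. A marker that acts only through baseline.** Its correlation with the follow-up score is ρr, and with the change score −(1 − ρ)r/√(2(1 − ρ)) = −r√((1 − ρ)/2). The chance of p < 0.05 follows from Fisher's z, with noncentrality atanh|c| × √(264 − 3).

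For r = 0.3:
- Follow-up: c = 0.18, noncentrality 2.940, Φ(2.940 − 1.960) = 84%.
- Change: c = −0.134, noncentrality 2.181, Φ(2.181 − 1.960) = 59%.

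| r | Follow-up score | Change score (opposite sign) |
|---|---|---|
| 0.1 | 16% | 11% |
| 0.2 | 50% | 30% |
| 0.3 | 84% | 59% |
| 0.4 | 98% | 83% |
| 0.5 | >99% | 96% |

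With baseline in the model the rate is the nominal 5%. A simulation of 3,000 trials at r = 0.3 gave 83%, 59% and 4.6%.

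Since 0.60 is itself a guess, the same formulas at r = 0.3 give:
- ρ = 0.4: 50% for follow-up (c = 0.12) and 76% for change (c = −0.164).
- ρ = 0.8: 98% for follow-up (c = 0.24) and 34% for change (c = −0.095).

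Neither score is safe over that range.

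**4. Moderator tests.** The standard error of a slope contrast between two arms of 88, per SD of predictor, is SD × √(2/88) = SD × 0.1508. The contrast detected with 80% power after baseline adjustment is (1.960 + 0.842) × 0.800 × 0.1508 = 0.338.
- Change score: 0.338/(0.894 × 0.1508) = 2.506, so power is Φ(2.506 − 1.960) = 71%.
- Follow-up score: 0.338/0.1508 = 2.241, so power is Φ(2.241 − 1.960) = 61%.

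This ignores the small part of the variance that the marker itself explains (0.18² = 3% at r = 0.3), so the follow-up figure is slightly low. In the step 3 simulation, false rejection of an interaction was 5.0% (follow-up), 4.9% (change) and 4.7% (adjusted).

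**5. Predictor-by-time in a mixed model.** With two complete time points and baseline treated as an outcome, the predictor-by-time coefficient is the change-score coefficient. In 400 simulated trials (r = 0.3, ρ = 0.60) the two agreed to rounding error. Both were rejected in 57% of trials, against 5% with baseline as a covariate.

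**The case against.** The strongest reply is that the article is silent, which is different from excluding baseline. The listed terms do not name arm main effects either, so the list need not be exhaustive. The Objectives call the moderator work exploratory, the statistical section calls its methods provisional, and an analysis plan not shown may give the covariates. The preceding subsection defines treatment response as change in total ADP-IV under mixed regression, which points away from a bare follow-up score.

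Much of this stands. A reader might infer that the plan deliberately omits baseline and discards the pre-post pairing on which the trial was sized. The documents do not support that: the pairing is lost only if the outcome is a follow-up score without baseline, and the sizing concerns treatment comparisons, not these models. A reader might also infer that the moderator findings would be biased or the Personalized Advantage Index distorted. Randomisation protects the interaction tests, and a predictor main effect common to all arms cancels from a linear between-arm contrast.

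It can also be said that a marker forecasting later severity through starting severity does predict outcome. That is true of outcome, but the stated target is response to treatment.

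What the reply does not remove is that the change reading fails too, at 59% for r = 0.3, and with the opposite sign. Nor does listing PD severity as a general predictor help, because it is not one of the four in these models.

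**Conclusion.** The point holds in a limited form. The article names the terms of these models without baseline ADP-IV and does not fix the form of the outcome. On either simple reading, a pure marker of starting severity can be declared a predictor of response far more often than 5% of the time, in opposite directions.

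The size depends on the unknown marker-baseline correlation: from 16% at 0.1 to over 99% at 0.5 with the follow-up score, and from 11% to 96% with the change score, at within-person correlation 0.60. For moderators the cost is power alone, from 80% to about 71% or 61%. The primary treatment comparison is not affected. The provisional status of the methods makes this a convenient moment to settle the wording, since leaving the score form to the time of analysis could decide the sign of a reported predictor.

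**What to change.** In the subsection on differential treatment response, state that the outcome is the follow-up ADP-IV score, and include baseline ADP-IV (same scoring) as a covariate in the single-predictor models, the multivariable model and the Personalized Advantage Index model. Define a predictor of response as an association with follow-up ADP-IV given baseline ADP-IV.

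If a mixed model is preferred, enter baseline ADP-IV as a covariate and use only the post-baseline scores as outcomes. A predictor-by-time test with baseline among the outcomes is no substitute, because it reproduces the change-score result (step 5).

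The cost is one sentence of text and one degree of freedom. Baseline assessment is completed before randomisation, so no further patients or measurements are needed.

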##### Mechanisms of change

It is hypothesized that the interventions exert a positive effect on the ADP-IV through their impact on the treatment-model-specific (i.e. insight ratings in SPSP, change in affect /defences/self-esteem ratings in APT and schema mode ratings in ST) and non-specific or common (i.e. alliance) mechanisms of change. To identify non-specific and specific mechanisms of change and the strength of the factors involved, both multilevel mediation models and structural equation models will be used. These analyses are based on the Latent Change Score models for mediation used in the research group of the Principal Investigator [19, 20].

#### Secondary study parameter(s)

##### (Differential) treatment response: secondary study parameters

We will examine change in the secondary outcome measures in the three treatments using mixed regression analysis. The secondary outcome measures include diagnostic status, reliable change and recovery, personality functioning, general functioning, general psychopathology, quality of life and happiness. As the PD severity indices AVPDSI, DPDSI and OCPDS vary per primary PD, they will be first standardized before they are analysed in the complete sample. This analysis will be controlled for primary PS, to account for possible differences in sensitivity to change. The underlying distribution of the mixed regression model will be determined based on the variable type (scale, nominal) and the distribution of residuals (e.g. normal, gamma, negative binomial). In addition, preliminary analyses will test differential treatment retention using survival analysis and mixed logistic regression. Medication confounds will be examined.

##### Cost-effectiveness

The cost-effectiveness analysis (CEA) will be conducted from a societal perspective. Within the CEA, the difference in societal costs (measured by the TiC-P at baseline and after 6, 12, 18, 24 and 36 months) generated by patients in the three treatments will be related to the difference in clinical effects (measured with the ADP-IV and quality-adjusted life-years based on the EQ-5D-5L) over the course of 36 months. Missing cost and effect data will be imputed using multiple imputation. Mixed model regression analyses will be used to estimate cost and effect differences between groups. Bootstrapping with 5000 replications will be used to estimate 95% confidence intervals around cost differences and the uncertainty surrounding the incremental cost-effectiveness ratios (ICERs). Uncertainty surrounding the ICERs will be graphically presented on cost-effectiveness planes. Cost-effectiveness acceptability curves [36] will also be estimated. Adjustment for confounders and effect modifiers will be done if necessary.

The statistical analyses described above are still under development and examples of possible methods. At the time of the analyses, we will use the optimal method for analysing the data.

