### Objectives {7}

The primary aim of this study is to compare the effectiveness and cost-effectiveness of the three individual treatments (SPSP, APT and ST) for Cluster-C PDs. The primary outcome of this superiority study is the severity of Cluster-C PD. We will compare the slopes over time of the three treatments from 0 to 12 months, with assessments of Cluster-C PD severity taking place at baseline, 1, 3, 6 and 9 months. Additionally, we will research differences between the outcomes of the three treatments at 18, 24 and 36 months follow-up. No hypothesis was formulated about the direction of a difference.

The second aim of this study is to explore working mechanisms by focussing on therapy-specific factors in the context of the contribution of common factors across psychotherapies. Selected therapy-specific factors are as follows: therapy-specific interventions; insight for SPSP; change in affect, defence style, perception of the self for APT; change in schema modes for ST. Working alliance is the non-specific factor being investigated.

The third aim is to identify general and specific predictors. Potential moderators will be studied exploratively. Firstly, we hypothesize that patients with relatively more childhood trauma will benefit more from ST than SPSP and APT, because of the use of imaginary rescripting, an evidence-based trauma processing technique [35, 83]. Secondly, we expect that patients with more severe personality pathology (e.g. borderline personality organization (Kernberg, [57]) will profit more from ST or SPSP than APT. This is because these therapies are developed and have proven their effectiveness for a broader range of PDs [60, 88], whereas APT is originally designed for the Cluster-C/neurotic population [25].

The relationship between specific treatment interventions, mediators and outcome will also be explored. Therapists will indicate per session which of the core interventions per treatment they have applied in their sessions. The hypothesis is that certain interventions will be stronger connected to mediators and outcome than others. For example, experiential techniques (imagery rescripting, multiple chair technique) for ST; adequate support for SPSP; facilitation of expression of emotions for APT.

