#### Costs

Treatment Inventory Cost in Psychiatric Patients (TiC-P, [97]). Societal costs are assessed using a specifically adapted version of the TiC-P. The TiC-P FORCE is a 14-item self-report questionnaire to assess health care costs (part I) and costs resulting from productivity losses (part II) associated with psychiatric disorders. In part I, the number of contacts with different health care providers over the last 6 months is assessed. Part II consists of items regarding absenteeism from paid and unpaid work and presenteeism (i.e. reduced productivity while at work) in the last 6 months.

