## Assignment of interventions: allocation

### Sequence generation {16a}

When patients are eligible for participation, the informed consent is signed and the baseline assessment is completed, they will be randomized to SPSP, APT or ST by the independent statistician, using computerized random assignment.^5^ Randomization of patients will be pre-stratified according to type of PDs (avoidant, obsessive, dependent, otherwise specified PD) and location (Amsterdam or Amersfoort). According to the treatment capacity, the randomization rate between SPSP, APT and ST can be adjusted if necessary.

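### Cost-effectiveness analysis: baseline costs and baseline utility should be fixed covariates, and the baseline cost questionnaire should be stated to lie outside the 36-month total

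*Protocol article*

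**What the plan says.** All references are to the Protocol article.

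- **Objectives {7}**: "The primary aim of this study is to compare the effectiveness and cost-effectiveness of the three individual treatments". The economic comparison is therefore part of the primary aim.
- **Cost-effectiveness** (under Statistical methods): the cost side is "the difference in societal costs (measured by the TiC-P at baseline and after 6, 12, 18, 24 and 36 months". The effect side is "measured with the ADP-IV and quality-adjusted life-years based on the EQ-5D-5L", and the horizon is "over the course of 36 months". Missing data are multiply imputed, cost and effect differences come from mixed models, and uncertainty comes from 5000 bootstrap replications. On covariates there is one sentence: "Adjustment for confounders and effect modifiers will be done if necessary". The section closes by calling the methods provisional.
- **Costs** (under Secondary outcomes): in part I of the TiC-P, "the number of contacts with different health care providers over the last 6 months is assessed". Part II covers absenteeism and "presenteeism (i.e. reduced productivity while at work) in the last 6 months".
- **Sequence generation {16a}**: once "the informed consent is signed and the baseline assessment is completed, they will be randomized to SPSP, APT or ST". Baseline therefore precedes allocation.

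**The concern.** Two features of the Cost-effectiveness section need attention.

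First, the baseline TiC-P stands in the same list as the five follow-up measurements, with no separate role. By its recall window and timing it can contain only costs incurred before any treatment was allocated. Its proper use is as a covariate, and the section does not say so.

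Second, the adjustment rule is framed around confounders and left conditional. In a randomised comparison, baseline differences arise by chance. The reason to adjust for baseline cost and baseline utility is that they predict later cost and later utility, whether or not the arms happen to differ. A rule that can be read as waiting for an observed imbalance gives up precision and leaves the choice of model to the time of analysis.

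The three arms are active therapies, so the true differences in cost and QALYs may well be small. Precision then largely decides whether the incremental ratios and acceptability curves are informative.

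**Working it through.** **1. What the baseline TiC-P covers.** With a 6-month recall at months 0, 6, 12, 18, 24 and 36, counted from randomisation, the windows are (−6, 0), (0, 6), (6, 12), (12, 18), (18, 24) and (30, 36). The first lies wholly before randomisation. The six windows add up to 6 × 6 = 36 months, but only 5 × 6 = 30 of these follow randomisation. A total that simply summed all six would match the horizon in length while containing the wrong months, so the article should say which windows count. (Months 24 to 30 fall in no window. That is a separate matter, and nothing below depends on it.)

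**2. QALY inputs.** The plan gives no precision figure for the economic analysis, so there is none to reproduce. From the document: 88 per arm (Sample size {14}) and a 36-month horizon. Assumed: EQ-5D-5L on the TiC-P schedule (Table 3 is not shown), utility SD 0.20, equal correlation r between any two time points, no dropout. The article's 0.60 is an educated guess for repeated assessments in the clinical sample size. It is not given for utilities, so r = 0.4 and 0.6 are shown as a range.

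**3. QALY formulas.** The trapezoid weights in years at 0, 6, 12, 18, 24 and 36 months are 0.25, 0.5, 0.5, 0.5, 0.75 and 0.5. They sum to 3.0, and their squares sum to 1.625.

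- Variance of the area under the curve, per unit utility variance: 1.625 + (3.0² − 1.625)r = 1.625 + 7.375r
- Covariance with baseline, per unit variance: 0.25 + 2.75r
- Standard error of a baseline difference: 0.20 × √(2/88) = 0.030
- Unadjusted standard error of the QALY difference: 0.030 × √variance
- Adjusted standard error: unadjusted × √(1 − R²), with R² = covariance²/variance
- Carry-over of a one-standard-error baseline difference: 0.030 × covariance

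| | r = 0.4 | r = 0.6 |
|---|---|---|
| Variance | 4.575 | 6.05 |
| Covariance with baseline | 1.35 | 1.90 |
| R² | 1.35²/4.575 = 0.398 | 1.90²/6.05 = 0.597 |
| Unadjusted SE (QALY) | 0.064 | 0.074 |
| Adjusted SE (QALY) | 0.050 | 0.047 |
| Reduction in SE | 22% | 36% |
| Carry-over (QALY) | 0.041 | 0.057 |

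**4. Sensitivity to decay.** Suppose instead that correlation is 0.6 between points 6 months apart and falls geometrically, so that baseline correlates 0.6, 0.36, 0.216, 0.130 and 0.047 with the later points. The covariance is then 0.25 + 0.5(0.6 + 0.36 + 0.216) + 0.75 × 0.130 + 0.5 × 0.047 = 0.959. The variance, from the same weights, is 4.123, so R² = 0.959²/4.123 = 0.223 and the standard error falls by 1 − √0.777 = 12%. Starting from 0.4 per 6 months, the same steps give covariance 0.583, variance 2.910, R² = 0.117 and a fall of 6%.

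**5. Costs.** Take equal variances and equal correlation ρ between 6-month cost windows. The sum of the five post-randomisation windows has variance 5 + 20ρ. Adjusting for the baseline window removes (5ρ)². The SD is therefore multiplied by √[(5 + 20ρ − 25ρ²)/(5 + 20ρ)]: 0.89 at ρ = 0.3, 0.69 at 0.6 and 0.49 at 0.8. Without adjustment, a chance baseline difference of 1 unit carries into the five-window total as 5ρ, that is 1.5, 3.0 or 4.0 units. The article gives no correlation for costs, so these ρ are assumptions.

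**The case against.** The strongest reply is that the fault is inferred. The list of TiC-P time points is a measurement schedule in parentheses. The same sentence confines the comparison to costs arising in the three treatments over 36 months, which pre-randomisation costs do not fit. Baseline costs have to be collected if they are to serve as a covariate. A mixed model can also use a baseline value as a time point or a covariate, and covariate lists for an economic analysis are commonly left to an analysis plan that is not shown here.

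Much of this stands. A reader might infer that six months of pre-treatment cost are added to the 36-month total, or that pre-treatment differences bias the comparison. The article supports neither: it nowhere says that baseline costs are summed, and randomisation leaves only chance differences. Nor is it an error that baseline utility enters the QALY, because it is the first point of the area under the curve.

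A reader might also want baseline ADP-IV added as a further covariate. The Objectives compare slopes from month 0 with baseline among the assessments, and the primary analysis concerns change in ADP-IV, so that model already uses baseline. No separate demand is warranted where the economic analysis takes its ADP-IV effect from that model.

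What does not fall away is the adjustment rule. The article states one, and it is weaker than one that costs nothing. Naming mixed models does not settle the matter for QALYs: if each patient's QALY is computed as a single area under the curve, baseline utility can adjust the comparison only as a covariate.

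**Conclusion.** The point holds as a free improvement, not as an error that invalidates the economic analysis. The baseline TiC-P covers only pre-randomisation months, the section lists it without a role, and adjustment for baseline values is left conditional. The consequence is lost precision, chance carry-over in the one trial realised, and a modelling choice left open in an analysis that belongs to the primary aim.

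Under equal correlation of 0.4 to 0.6, utility SD 0.20, EQ-5D-5L on the TiC-P schedule and 88 per arm, adjustment lowers the standard error of the 36-month QALY difference by about 22 to 36%. The percentage does not depend on the SD or the sample size. It does depend on the correlation pattern and the visit schedule: geometric decay from the same starting values gives 6 to 12%. For costs the direction is the same, and the size rests wholly on an unknown correlation.

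**What to change.** In the Cost-effectiveness section, or in the analysis plan that it leads to:

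1. State that the baseline TiC-P is not part of the 36-month cost total.
2. Enter baseline TiC-P cost as a prespecified covariate in the cost model, always.
3. Enter baseline EQ-5D-5L utility as a prespecified covariate in the QALY model, always.
4. Apply both adjustments within each imputed data set and each bootstrap replicate, so that the ratios, planes and acceptability curves rest on the adjusted differences.
5. Remove the conditional wording for these two covariates. It may stay for others.

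No baseline ADP-IV covariate need be added where that effect comes from the change or slope mixed model.

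The cost is a few sentences of analysis text. Baseline costs are already scheduled, and baseline utility is needed for the QALY calculation in any case. The sample size and visits are unchanged.

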**Methods:**

This is a mono-centre randomized clinical trial with three parallel groups: (1) SPSP, (2) APT, (3) ST. Randomization on patient level will be pre-stratified according to type of PD. The total study population to be included consists of 264 patients with Cluster-C PDs or other specified PD with mainly Cluster-C traits, aged 18–65 years, seeking treatment at NPI, a Dutch mental health care institute specialized in PDs. SPSP, APT and ST (50 sessions per treatment) are offered twice a week in sessions of 50 min for the first 4 to 5 months. After that, session frequency decreases to once a week. All treatments have a maximum duration of 1 year. Change in the severity of the PD (ADP-IV) will be the primary outcome measure. Secondary outcome measures are personality functioning, psychiatric symptoms and quality of life. Several potential mediators, predictors and moderators of outcome are also assessed. The effectiveness study is complemented with a cost-effectiveness/utility study, using both clinical effects and quality-adjusted life-years, and primarily based on a societal approach. Assessments will take place at baseline, start of treatment and at 1, 3, 6, 9, 12, 18, 24 and 36 months.

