### Provisions for post-trial care {30}

Patients who drop out from treatments will be referred for regular clinical care. During the follow-up period, no specific interventions are offered. Patients are referred to their general practitioner if clinically necessary. Patients can apply for additional treatment 6 months after treatment termination (18 months after start treatment) with a referral from their general practitioner. In case of additional treatment, patients will not return to the same therapist.

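### The cost questionnaire's 6-month recall, given at 24 and then at 36 months, leaves months 24 to 30 unreported, so the 36-month cost-effectiveness result rests on an unstated assumption

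*Protocol article*

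**What the plan says.** All references are to the protocol article.

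- **Instrument (Costs).** "Societal costs are assessed using a specifically adapted version of the TiC-P". It is the only instrument described for societal costs.
- **Recall.** In part I, "the number of contacts with different health care providers over the last 6 months is assessed". Part II covers "absenteeism from paid and unpaid work and presenteeism (i.e. reduced productivity while at work) in the last 6 months". No exception is made for any assessment.
- **Schedule (Statistical methods {20a}, Cost-effectiveness).** Costs are "measured by the TiC-P at baseline and after 6, 12, 18, 24 and 36 months".
- **Horizon (same section).** Cost differences are related to differences in ADP-IV and quality-adjusted life-years "over the course of 36 months".
- **Visits (abstract, Methods).** "Assessments will take place at baseline, start of treatment and at 1, 3, 6, 9, 12, 18, 24 and 36 months". Nothing falls between 24 and 36 months.
- **Missing costs (Cost-effectiveness).** Multiple imputation is planned, followed by mixed models and bootstrapping. No separate rule is given for an interval that no form covers.
- **Later care (Provisions for post-trial care {30}).** "Patients can apply for additional treatment 6 months after treatment termination (18 months after start treatment".

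**The concern.** Recall period, schedule and horizon are each stated, and they do not fit together. Up to month 24 the forms are 6 months apart and the 6-month windows join. The last interval is 12 months and the window is still 6, so the first half of year 3 drops out.

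This is a matter of data collection. A later analysis plan can add an assumption for the gap, but it cannot produce reports that were never requested.

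Effects do not suffer in the same way. A utility is a state at one point in time, and values at 24 and 36 months can be joined to give quality-adjusted life-years (assuming that the EQ-5D-5L is given at both; the schedule table is not shown). A resource count is a total over its own window and says nothing about the preceding half-year.

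Cost-effectiveness is part of the primary aim (Objectives {7}). All arms are planned to receive the same number and length of sessions, so cost differences will come largely from incomplete treatment, other care and lost productivity. The questionnaire is the only described source for the last two. Further treatment is possible from month 18, so costs in the gap cannot be presumed zero or equal between arms.

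**Working it through.** **Inputs.** Forms at t = 0, 6, 12, 18, 24 and 36 months and a 36-month horizon (Cost-effectiveness). Recall of 6 months (Costs). Completion allowed within 2 weeks either side, about 0.5 month (Plans to promote participant retention {18b}).

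**Step 1: coverage.** A form at month t covers t − 6 to t.

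| Form at month | Window covered | Months inside the horizon |
|---|---|---|
| 0 | −6 to 0 | 0 |
| 6 | 0 to 6 | 6 |
| 12 | 6 to 12 | 6 |
| 18 | 12 to 18 | 6 |
| 24 | 18 to 24 | 6 |
| 36 | 30 to 36 | 6 |

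Total: 5 × 6 = 30 of 36 months (83.3%). The stated 36 months is not reached. Uncovered: months 24 to 30, which is 6/36 = 16.7% of the horizon and 6/12 = half of year 3.

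**Step 2: does the completion window close the gap?** Gap = (time of last form − 6) − time of 24-month form.

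- Smallest: (35.5 − 6) − 24.5 = 5 months.
- Largest: (36.5 − 6) − 23.5 = 7 months.

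It never closes.

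**Step 3: what the gap does to the cost difference.** Let d be a constant monthly cost difference between two arms. The true 36-month difference is 36d.

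- *Gap counted as zero:* 30d is obtained. The shortfall is 6d/36d = 16.7%.
- *Gap filled with the mean of the two neighbouring windows:* (6d + 6d)/2 = 6d, so the total is 30d + 6d = 36d. There is no bias.
- *Differences not constant:* the error from the same filling rule is [D(18–24) + D(30–36)]/2 − D(24–30), where D is the difference accrued in each window. It may have either sign. If a difference arises only in months 24 to 30, all of it is missed.

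No questionnaire data bear on D(24–30), so the trial cannot show which case applies.

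**Step 4: can imputation supply it?** Multiple imputation learns a missing value from patients in whom it was observed, and here there are none. A longitudinal model could still return a figure for month 30, but that figure would come from the assumed shape of costs over time.

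**Step 5: remedies by the same arithmetic.** A form at month 30 gives 36 of 36 months. A 12-month recall at month 36 gives 24 + 12 = 36 of 36. A 24-month horizon gives 24 of 24.

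**The case against.** The strongest reply is that the article never says how costs are accumulated. It plans mixed models, calls its methods provisional, and may leave the treatment of a 12-month interval to an analysis plan that is not shown. This stands against stronger readings that a reader might infer:

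- **That the 36-month ratios are wrong as planned, or that 30 months of costs will be set against 36 months of effects.** The article contains no rule that sums the windows and counts the gap as zero.
- **That the cost difference is understated by 17%, or by up to half of its year-3 part.** The 17% needs zero-filling and a constant difference; interpolation under that constancy removes it. Half is no upper limit: under zero-filling the loss of a year-3 difference runs from none (all of it in months 30 to 36) to all (all of it in months 24 to 30).
- **That the gap is precisely when re-treatment costs appear.** Further treatment is possible from month 18, and months 18 to 24 are fully covered, as are 30 to 36. Nothing singles out the half-year between. A gap common to all arms biases the difference only if the arms differ there in a way that the chosen filling rule does not capture.
- **That no information of any kind exists for these months.** Electronic patient records are named as a data source (Plans for assessment and collection of outcomes {18a}) and might recover care given at the institute. The text does not link them to costs, and they would not be expected to hold productivity loss or care elsewhere.

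The questionnaire is also an adapted version and the schedule table is not shown, so a longer recall at month 36 cannot be excluded. The text, however, states 6 months without exception.

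The reply does not remove the gap itself. However costs are modelled, no patient is asked about months 24 to 30, and no assumption for them is stated.

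**Conclusion.** The point holds in limited form. On the stated recall and schedule, the questionnaire covers 30 of the 36 months. Months 24 to 30 are unreported by design for every patient in all three arms. The 36-month cost differences and cost-effectiveness ratios therefore depend on an assumption that the article does not state. Neither the size nor the direction of any bias can be given; the 17% is an illustration under zero-filling and a constant difference.

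The conclusion assumes that the 6-month recall applies at month 36 as written. The primary clinical comparison (ADP-IV slopes over 0 to 12 months) and the sample size are unaffected. This should be fixed before the cost data are analysed, but it does not threaten the main trial result.

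**What to change.** 1. **Close the gap where still possible.** Either extend the recall of the month-36 form to 12 months, or give the 14-item online form at month 30 to patients who have not passed it. The longer recall is less accurate and would mix recall periods if some patients have already completed month 36. The extra form costs one short questionnaire per patient.
2. **For patients already past that point, prespecify the filling rule.** Recruitment began in October 2020, so counting from inclusion the earliest patients reach month 30 around April 2023, and a change may come too late for them. One option is the mean of the 18–24 and 30–36 month windows, with sensitivity analyses that vary this assumption, including by arm. Institute records could check part of the health care component.
3. **Report a 24-month cost-effectiveness result alongside the 36-month one.** Its cost windows are complete by design, and it needs no new data.
4. **If the adapted form already asks about 12 months at month 36,** correct the Costs section to say so; the gap then disappears.

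Items 2 to 4 cost only text and analysis time.
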